### 6.8 AnapnoGuard 100 System Disconnection

Prior to disconnection, during weaning from mechanical ventilation, the following will be evaluated:

- Level of sedation according to the Richmond Agitation Sedation Scale (RASS).
- Duration of the weaning process and medications usage and dosages.

After extubation, all patients will be scanned by chest x-ray.

During 48 hours following extubation, the following parameters will be used for evaluation of possible mechanical complications:

- - Throat pain level, associated with the mechanical ventilation. Pain level will be assessed by VAS (visual analogue scale) questionnaire.
  - Hoarseness occurrence
  - Spirometry analysis
  - Fiber optic analysis (this measure will be used in selected ICUs)
  - VAP Occurrence

# 7. DeVICE MAINTENENCE AND DISPOSAL

The AnapnoGuard endotracheal tube ETT and the connection kit are sterile, singe use components, which need to be properly disposed after extubation.

The AnapnoGuard 100 system should be disinfected and cleaned after each patient according to Hospitech Respiration LTD instructions.

# 8. Statistical Consideration

## 8.1 Safety Analysis Set

The safety analysis set will consist of all subjects for whom the study treatment was initiated. AE's will be tabulated by treatment arm, severity and relation to treatment.

## 8.2 Sample Size considerations

Presentation of sample size is based on achieving 80% power overall to demonstrate that the *rate of AE and SAE as a result of using AnapnoGuard 100 during mechanical intubation* is up to 0.15. Thus, the determination of sample size in this trial will be based on *rate of AE and SAE as a result of using AnapnoGuard 100 during mechanical intubation*.

A former study using *AnapnoGuard 100* during mechanical intubation revealed no related AE or SAE during intubation (all together 29 patients were studied). Consequently, we feel that 80% (of study patients with no AE or SAE) to be an appropriate clinical target for AnapnoGuard 100 success rate. Assuming a true success rate of 80%, a sample of **N = 25** will provide 80% power to show that AnapnoGuard 100 success (no AE or SAE during intubation) is at least 80%. This is based on a power analysis using the normal approximation for the binomial, with one-sided Alpha=0.05.

As control treatment is assumed to have the same success rate (at least 80% cases with no AE or SAE during intubation), therefore same number of patients will be recruited to the control group **(N=25).**

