| **Definition of the safety of AnapnoGuard system** | This study has primary endpoint - *rate of AE and SAE as a result of using AnapnoGuard 100 during mechanical intubation.* Thus, a subject's responsiveness is evaluated as following:   - A subject is considered a “success “on *safety* if no device related AE or SAE has occurred during intubation. |
| **Sample size** | Presentation of sample size is based on achieving 80% power overall to demonstrate that the *rate of AE and SAE as a result of using the AnapnoGuard 100 during mechanical intubation* is up to 0.20. Thus, the determination of sample size in this trial will be based on *rate of AE and SAE as a result of using AnapnoGuard 100 during mechanical intubation*.  A former study using *AnapnoGuard 100* during mechanical intubation in ICU revealed **no related AE or SAE** (all together 29 patients were studied). Consequently, we feel that 80% (of study patients with no AE or SAE during intubation) to be an appropriate clinical target for AnapnoGuard 100 success rate. Assuming a true success rate of 80%, a sample of **N = 25** will provide 80% power to show that AnapnoGuard 100 success (no AE or SAE during intubation) is at least 80%. This is based on a power analysis using the normal approximation for the binomial, with one-sided Alpha=0.05.  As control treatment is assumed to have the same success rate (at least 80% cases with no AE or SAE during intubation), same number of patients will be recruited to the control group **(N=25)**  To account for an approximate 15% dropout rate, we set a total number of patients N=**60** (for study and control groups together). |
| **Primary endpoint and study hypothesis** | For the primary endpoints we will compute Overall Proportion of Success:    The following hypotheses are specified:  The safety proportion of success (*No AE or SAE while using AnapnoGuard 100 during intubation* -R):  H0: R < 0.80  H1: R > 0.80  This hypotheses will be tested by:   1. Constructing a one-sided, lower 95% confidence interval about the observed Overall Proportion of Success in the relevant cohort; 2. Examining whether the lower limit of the confidence interval is at or above the success criterion   Study success will be declared if the following is met:  Lower confidence limit of *No* *device related AE and SAE as a result of using AnapnoGuard 100 during mechanical intubation* success rate is at 0.80 or above |

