## To account for an approximate 15% dropout rate, we set a total number of patients N=60 (for study and control groups together).

## 8.3 Statistical Analysis

Safety of the AnapnoGuard 100 system will be evaluated by rate of AE or SAE during intubation in ICU. It is assumed that no AE or SAE will be detected wile using AnapnoGuard 100 during intubation in ICU in at least 80% of study patients.

Study hypothesis is stated in terms of Overall Proportion of Success (no AE or SAE), which is computed by total number of successes on the parameter divided by the total number in its respective cohort.

The following hypothesis is specified and will be tested:

The safety proportion of success (No AE or SAE while using AnapnoGuard 100 during intubation -R):

H0: R < 0.80

H1: R > 0.80

This hypothesis will be tested by:

1. Constructing a one-sided, lower 95% confidence interval about the observed Overall Proportion of Success in the relevant cohort
2. Examining whether the lower limit of the confidence interval is at or above the success criterion

Study success will be declared if the following is met:

1. Lower confidence limit of *rate of AE and SAE as a result of using AnapnoGuard 100 during mechanical intubation* success is at 0.80 or above.

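### Section 8.2 sizes the trial to show an event rate of up to 0.15, against 0.20 in the synopsis and an 80% success threshold everywhere else

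*Protocol*

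**What the plan says.** Protocol 8.2 says the trial is sized to demonstrate that the event rate "is up to 0.15. Thus, the determination of sample size in this trial will be based on" that rate. The corresponding sentence in the Study Synopsis (Sample size) is otherwise almost identical, but there the rate "is up to 0.20. Thus, the determination of sample size in this trial will be based on" the same quantity.

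The next paragraph of 8.2 takes 80% event-free patients "to be an appropriate clinical target for AnapnoGuard 100 success rate". It then sets out the calculation: "Assuming a true success rate of 80%, a sample of" 25 is said to give 80% power to show success of at least 80%, "using the normal approximation for the binomial, with one-sided Alpha=0.05".

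Section 8.3 gives H0 as R below 0.80 and H1 as R above 0.80. The test is done by "Constructing a one-sided, lower 95% confidence interval about the observed Overall Proportion of Success in the relevant cohort", and the trial succeeds if the lower limit for "success is at 0.80 or above". The synopsis states the same hypotheses and the same limit.

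**The concern.** The largest acceptable event rate is the central design parameter of a single-threshold safety test. The protocol states it in two incompatible ways. A rate of up to 0.15 means success of at least 0.85; a rate of up to 0.20 means success of at least 0.80. Both figures are current text: the protocol shows deleted wording struck through in 4.1, 4.2 and 6.1, and neither figure is struck through.

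Section 8.2 also disagrees with itself, since its first paragraph implies 0.85 and its second works with 80%. A reader who takes the opening of 8.2 as the aim would expect the trial to show something stricter than the rule in 8.3 requires. With about 25 to 30 patients in the device arm, five percentage points in the threshold is a visible difference.

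**Working it through.** **Step 1. The thresholds side by side, on the success scale.**

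| Place | As stated | Success threshold |
|---|---|---|
| 8.2, opening sentence | event rate up to 0.15 | 1 − 0.15 = 0.85 |
| Synopsis, Sample size | event rate up to 0.20 | 1 − 0.20 = 0.80 |
| 8.2 and synopsis, clinical target | 80% success | 0.80 |
| 8.2 and synopsis, power statement | success at least 80% | 0.80 |
| 8.3 and synopsis, H0 and H1 | R against 0.80 | 0.80 |
| 8.3 and synopsis, success rule | lower limit at 0.80 or above | 0.80 |

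Only the opening sentence of 8.2 stands apart. The synopsis 0.20 and the 0.80 elsewhere are complements, so they are one threshold.

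**Step 2. Does either figure reproduce N=25?** Inputs from 8.2: one-sided alpha 0.05 (z = 1.645), power 80% (z = 0.842), assumed true rate p1 = 0.80, n = 25. With threshold p0, normal-approximation power is

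Φ{ [(p1 − p0)√n − 1.645√(p0(1−p0))] / √(p1(1−p1)) }.

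- p0 = 0.80: the first term is zero, so power = Φ(−1.645) = 0.05, not 0.80. Exact power, passing at 24/25, is 0.027.
- p0 = 0.85: the assumed true rate is below the threshold. Exact power, passing at 25/25, is 0.004.
- Reading 0.15 as the expected event rate (p1 = 0.85) against p0 = 0.80: n = [(1.645 × 0.400 + 0.842 × 0.357)/0.05]² ≈ 368 with the null variance in the alpha term, or 0.85 × 0.15 × (2.486/0.05)² ≈ 316 with the alternative variance throughout. Neither is 25.

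So N=25 does not show which figure was intended.

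**Step 3. What the difference would do to the pass count.** The protocol names no interval method, so three were tried. The figures are one-sided lower 95% limits for n = 25.

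| Successes | Exact (Clopper-Pearson) | Wilson | Wald (normal approximation) |
|---|---|---|---|
| 23/25 | 0.769 | 0.785 | 0.831 |
| 24/25 | 0.824 | 0.839 | 0.896 |
| 25/25 | 0.887 | 0.902 | 1.000 |

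A threshold of 0.80 needs 24 (exact, Wilson) or 23 (Wald). A threshold of 0.85 needs 25 or 24 respectively. Under each method the stricter threshold costs one patient. The same holds at n = 30, half of the planned 60: exact or Wilson 28 against 29, Wald 27 against 28.

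**Step 4. What it would do to power (exact limit, n = 25).** For threshold 0.80, power = P(X ≥ 24) = p²⁵ + 25(1−p)p²⁴. For 0.85, power = p²⁵. The true rates below are assumptions; the protocol gives none above 0.80.

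| Assumed true success rate | Threshold 0.80 | Threshold 0.85 |
|---|---|---|
| 0.90 | 0.072 + 0.199 = 0.27 | 0.07 |
| 0.95 | 0.277 + 0.365 = 0.64 | 0.28 |
| 0.97 | 0.467 + 0.361 = 0.83 | 0.47 |

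**The case against.** The best defence is that 0.15 does no work. It appears once, in the sentence introducing the sample-size rationale, and in no hypothesis, interval step or success criterion. The rest of 8.2 uses 80%, so 0.15 looks like a leftover or a typing error. That is largely right, and it limits the finding.

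A reader might infer that the pass mark is undefined, that two maximum rates govern the decision, or that a result between the thresholds could be reported either way once the data are known. The protocol does not support this. The rule is given twice with the same limit of 0.80. A result whose lower limit falls between 0.80 and 0.85 meets the only written criterion, and calling it a failure would need a rule the protocol does not contain.

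The size of the effect is also open to challenge. The true rates in Step 4 are not in the protocol, and the exact limit is a choice. For example, 28/30 has an exact lower limit of 0.805, which passes 0.80 and fails 0.85, but its Wald limit is 0.858, which passes both.

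What remains is the contradiction itself. The protocol says its sample size rests on this rate, and the two places that state the rate disagree.

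**Conclusion.** The contradiction holds. Section 8.2 gives a maximum event rate of 0.15 where the synopsis gives 0.20 and every other statement of the threshold is 80% success. The fault is one inconsistent design threshold in the sample-size statement. The decision rule is legible and consistent at 0.80.

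If 0.85 were really meant, the trial would need one more success to pass under any of the three interval methods tried. With an exact limit, n = 25 and assumed true rates from 0.90 to 0.97, power would fall by about 20 to 36 percentage points. These figures are illustrations under stated assumptions, not properties the protocol fixes.

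A separate and larger fault sits in the same paragraph: the assumed true rate equals the threshold, so power at N=25 is about 5% by normal approximation, not 80%. Correcting 0.15 leaves that untouched.

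**What to change.** Change 0.15 to 0.20 in the opening sentence of 8.2, before any data are reviewed. This costs one figure and brings 8.2 into line with the synopsis, its own target, the hypotheses and the success rule.

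If 0.15 was intended, the change is wider. The synopsis rate, the 80% target and power statement in the synopsis and 8.2, the 80% assumption in 8.3, and H0, H1 and the success limit in the synopsis and 8.3 must all move to 0.15 or 0.85. Power must then be restated for that rule.

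On either route the power statement for N=25 needs its own correction, with an assumed true success rate above the threshold.

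### The power statement assumes a true success rate equal to the 0.80 threshold being tested, so the stated 80% power is impossible at any sample size; by the plan's own method it is about 5%

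*Protocol*

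**What the plan says.** Protocol section 8.2 sets the sample size for the AnapnoGuard arm. It begins "Assuming a true success rate of 80%, a sample of" N = 25, and continues that this sample "will provide 80% power to show that AnapnoGuard 100 success (no AE or SAE during intubation) is at least 80" per cent. The method is given: "This is based on a power analysis using the normal approximation for the binomial, with one-sided Alpha=0.05". The synopsis repeats the argument.

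Section 8.3, again matched by the synopsis, sets H0: R < 0.80 against H1: R > 0.80, where R is the proportion of patients counted as a safety success. The test has two steps: "Constructing a one-sided, lower 95% confidence interval about the observed Overall Proportion of Success in the relevant cohort", then "Examining whether the lower limit of the confidence interval is at or above the success criterion". The criterion is 0.80. No interval method is named.

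The sample size text ends: "To account for an approximate 15% dropout rate, we set a total number of patients N=60" for both groups together, so 30 per arm. The target event rate in the opening sentence of 8.2 is up to 0.15; the matching sentence in the synopsis has up to 0.20.

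**The concern.** Power is the chance of meeting the success criterion when the truth lies in the alternative. Here the truth used for planning, 0.80, is the threshold itself and does not satisfy H1: R > 0.80. With no distance between the assumed rate and the threshold, a larger sample cannot raise the chance of success.

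This power calculation is the only justification given for N, and the 0.80 criterion is the only formal success test in the protocol. A reader who relies on the 80% figure would take the trial as likely to succeed if the device just meets its target. In that case it would nearly always fail. The protocol also gives no sign of how few failures the criterion tolerates, or how high the true success rate must be for a good chance of passing.

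**Working it through.** **Inputs.** From 8.2: assumed true rate p1 = 0.80, n = 25, one-sided alpha 0.05, normal approximation. From 8.3: threshold p0 = 0.80, success if the one-sided 95% lower limit is at least 0.80. From the end of 8.2: 15% dropout, 60 patients in total. The dropout step is consistent: 25 / 0.85 = 29.4, so 30 per arm.

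**1. The plan's own figure.** The one-sample normal approximation is

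power = Φ{ [ (p1 − p0)√n − 1.645 √(p0(1 − p0)) ] / √(p1(1 − p1)) }.

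With p1 = p0 = 0.80, the first term is 0 and both square roots are 0.4. So power = Φ(−1.645) = 0.050 for every n. The stated 80% is not reproduced. Two-sided alpha gives 2.5%, and a continuity correction gives 2.9% at n = 25.

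**2. Exact probability of passing at a true rate of 0.80.** The result depends on the interval.

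| Interval | n | Fewest successes that pass (lower limit) | Probability of passing at R = 0.80 |
|---|---|---|---|
| Clopper-Pearson | 25 | 24 (0.824) | 2.7% |
| Clopper-Pearson | 30 | 28 (0.805) | 4.4% |
| Uncorrected Wald | 25 | 23 (0.831) | 9.8% |
| Uncorrected Wald | 30 | 27 (0.810) | 12.3% |

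Wilson and Agresti-Coull limits give the same cut-offs as Clopper-Pearson at these two sizes. The Wald figures exceed 5% because that interval fails to hold its nominal level here; they are not genuine power.

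**3. What N = 25 could support.** Solving the formula in step 1 for 80% power with p0 = 0.80 and n = 25 gives p1 ≈ 0.963. Check: (0.1633 × 5 − 1.645 × 0.4) / √(0.9633 × 0.0367) = (0.8165 − 0.6579) / 0.1880 = 0.843, and Φ(0.843) ≈ 0.80. With the exact limit the required rate is 0.967 at n = 25 and 0.948 at n = 30. The protocol states none of these rates.

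N = 25 also comes out of (1.645 + 0.842)² × 0.80 × 0.20 / (0.80 − 0.60)² = 24.7, that is, a true rate of 0.80 against a threshold of 0.60. The protocol contains no threshold of 0.60, so this cannot be taken as the intended design.

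**4. The 0.15 event rate in 8.2.** Read as a success threshold of 0.85, it puts the assumed 0.80 inside the null: Φ{[(0.80 − 0.85) × 5 − 1.645 × √(0.85 × 0.15)] / 0.4} = Φ(−2.09) = 1.8%. It does not rescue the statement.

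**5. Power across evaluable n** (exact Clopper-Pearson limit; the true rates 0.95 and 0.90 are illustrative assumptions, not protocol figures).

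| Evaluable n | Failures allowed | Power, true 0.95 | Power, true 0.90 |
|---|---|---|---|
| 25 | 1 | 64% | 27% |
| 26 | 1 | 62% | 25% |
| 27 | 1 | 61% | 23% |
| 28 | 1 | 59% | 22% |
| 29 | 1 | 57% | 20% |
| 30 | 2 | 81% | 41% |

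Two failures in 29 give a lower limit of 0.798, just short. Losing one patient of 30 therefore costs more than a fifth of the power at a true rate of 0.95.

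**The case against.** The strongest reply is that the sample may still be adequate. The pilot is cited as showing no related events in 29 patients. If the true success rate is 0.967 or higher, 25 patients give at least 80% exact power. That stands. A reader might infer that the trial is too small, and the documents do not support that inference: they show a wrong justification and no stated alternative. Nor does the pilot prove adequacy. The one-sided 95% lower limit for 29 successes in 29 is 0.05^(1/29) = 0.90, and at that rate exact power is 20% to 41%.

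A reader might also infer that power is at most 5%, or that exactly one failure in 25 and two in 30 are allowed. Both hold for an exact limit. The protocol names no interval, a choice often left to the SAP, and a Wald limit would allow two and three failures. The firm statement is about 5% by the plan's own method, with 2.7% to 12.3% at n = 25 or 30 across the intervals examined.

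It could be said that the pilot contradicts a true rate of 0.80. But 8.2 uses the pilot to support 80% as a clinical target, not as an estimate of the true rate. The fault is that the same 80% is then used as the assumed truth.

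**Conclusion.** The point holds as an error in the power statement. Under the assumption written in 8.2 and the synopsis, the probability of declaring success is 5% by the stated method, not 80%, and no sample size changes that. No interval examined brings it near 80%.

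The conclusion rests only on the protocol's assumed rate, threshold, alpha and decision rule. The exact figures assume independent patients and the evaluable numbers shown. Whether N is sufficient cannot be judged until the sponsor states the success rate it expects.

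**What to change.** Keep N = 60, and make these changes:

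- **8.2 and synopsis:** delete the sentence that claims 80% power at a true rate of 80%. State an alternative success rate above 0.80, mark it as the sponsor's assumption and justify it. Justify it for the events that count: 3.1 counts device-related events only, while 8.3 words the hypothesis as no AE or SAE.
- **8.3 and synopsis:** name the exact (Clopper-Pearson) one-sided 95% lower limit as the basis for the decision.
- **8.2:** give the pass rule and exact power for every plausible evaluable n: at most one failure for n = 25 to 29 and at most two for n = 30. Quoting only n = 25 and n = 30 would hide the fall between them. The table in step 5 can be used, with 0.95 and 0.90 replaced or supplemented by the sponsor's own rate.
- **8.2 against synopsis and 8.3:** reconcile the 0.15 event rate with 0.20 and with the 0.80 criterion.

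The cost is wording only, with no added patients. The price is a less favourable stated power: at a true rate of 0.95 it reaches 80% only if all 30 patients are evaluable.

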## To account for an approximate 15% dropout rate, we set a total number of patients N=60 (for study and control groups together).

## 8.3 Statistical Analysis

Safety of the AnapnoGuard 100 system will be evaluated by rate of AE or SAE during intubation in ICU. It is assumed that no AE or SAE will be detected wile using AnapnoGuard 100 during intubation in ICU in at least 80% of study patients.

Study hypothesis is stated in terms of Overall Proportion of Success (no AE or SAE), which is computed by total number of successes on the parameter divided by the total number in its respective cohort.

The following hypothesis is specified and will be tested:

The safety proportion of success (No AE or SAE while using AnapnoGuard 100 during intubation -R):

H0: R < 0.80

H1: R > 0.80

This hypothesis will be tested by:

1. Constructing a one-sided, lower 95% confidence interval about the observed Overall Proportion of Success in the relevant cohort
2. Examining whether the lower limit of the confidence interval is at or above the success criterion

Study success will be declared if the following is met:

1. Lower confidence limit of *rate of AE and SAE as a result of using AnapnoGuard 100 during mechanical intubation* success is at 0.80 or above.

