| **Patient selection criteria** | **Inclusion Criteria**  Subjects eligible for this clinical study must fulfill **all** of the following:   1. Age above 21 (men and woman); 2. Patient is admitted to ICU and expected to receive mechanical ventilation for more than 12 hours; 3. Absence of clear signs of pneumonia and lung contusion on chest X ray; 4. Connection of the ETT to the AnapnoGuard system less than 6 hours from intubation initiation; 5. No fever or fever from known from other non chest/lung origin;     **Exclusion Criteria**  Subjects not eligible for this research study include those that **have any** of the following:   1. Patients who had been treated with mechanical ventilation during the last 3 months; 2. Patients with facial, oropharyngeal or neck trauma 3. BMI>40 4. Pregnant women 5. Patient ventilated in prone position  Difficult intubation (defined as more than 3 intubation attempts) |
| **Primary objectives** | The study primary objective is:   - Evaluation of the safety of using the AnapnoGuard 100 system during the course of mechanical ventilation and intubation in Intensive Care Unit (ICU); |
| **Secondary objectives** | The study secondary objectives are   - Evaluate the occurrence of mechanical complication due to ETT cuff over inflation. - Physician satisfaction from AnapnoGuard 100 system |
| **Primary outcome measures** | Primary safety outcome measure in this study is:   - Rate of AE (adverse events) and SAE (serious adverse events) while using the AnapnoGuard 100 system during the course of mechanical ventilation and intubation in Intensive Care Unit (ICU). |
| **Secondary outcome measures** | - - Mechanical complication occurrence due to ETT cuff over inflation will be evaluated by the following measures during the 48 hours post extubation:   - Throat pain level, associated with the mechanical ventilation. Pain level will be assessed by VAS (visual analogue scale) Scale;   - Hoarseness occurrence   - Spirometry analysis   - Fiber optic analysis (this measure will be used in selected ICUs) - Medical staff satisfaction from AnapnoGuard 100 system will be established by designated questionnaire. |
| **Other Observation** | - Evaluation of the effect of AnapnoGuard system upon ventilator associated pneumonia (VAP) occurrence rate and time to VAP in intubated patients in intensive care units (ICU). |

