# 3. ENDPOINT PARAMETERS

## 3.1 Primary Endpoint Parameter

This study has primary endpoint - *rate of device related AE and SAE as a result of using AnapnoGuard 100 during mechanical intubation.* Thus, a subject's responsiveness is evaluated as following:

- A subject is considered a “success “on *safety* if no device related AE or SAE has occurred during intubation.

Serious adverse event are defined as adverse requiring operation and/or associated with prolongation of hospital stay. Serious adverse events occurrence will be compared to serious adverse events incidence in the control group of mechanically ventilated patients in intensive care units.

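### The primary endpoint counts device-related events in some places and any AE or SAE in others, no text says which governs, and the choice can decide the trial

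*Protocol*

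**What the plan says.** Device-related events only:
- Section 3.1 calls a subject a success "if no device related AE or SAE has occurred during intubation". The synopsis row defining safety uses the same sentence.
- The synopsis success rule takes the lower confidence limit of the proportion with no "device related AE and SAE as a result of using AnapnoGuard 100 during mechanical intubation".

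Any event:
- The synopsis primary outcome measure is "Rate of AE (adverse events) and SAE (serious adverse events) while using the AnapnoGuard 100 system". The synopsis hypothesis likewise defines R without a relatedness qualifier.
- Section 8.3 opens its analysis with "Safety of the AnapnoGuard 100 system will be evaluated by rate of AE or SAE during intubation in ICU" and continues: "Study hypothesis is stated in terms of Overall Proportion of Success (no AE or SAE"). Its R is again unqualified.

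Mixed:
- Section 8.2 bases the sample size on events attributable to the device and supports the target with a pilot that reported no related events. It then states the target as freedom from AE or SAE, with no qualifier. Its control assumption is also unqualified: "As control treatment is assumed to have the same success rate (at least 80% cases with no AE or SAE during intubation").
- The 8.3 success rule goes back to attributable events. As written, it asks for the lower limit of the "rate of AE and SAE as a result of using AnapnoGuard 100 during mechanical intubation" success to be at least 0.80, which joins an event rate to a success criterion.

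**The concern.** Study success rests on a single proportion and a fixed bar of 0.80. The protocol defines that proportion in two ways and ranks neither above the other. In ventilated ICU patients, a count of all adverse events and a count of device-related ones can differ widely. The 9.2 definition of a serious event includes death and life-threatening events, and the 9.3 list includes mild events such as a leak detected by the ventilator.

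The trial is open label. If the definition is settled after events have accrued, it can be settled with knowledge of the result. An analysis plan cannot cure this alone, because following either definition would contradict part of the protocol.

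The attributable wording causes a further difficulty for the control arm. Section 3.1 asks for serious events to be compared with control, but an event caused by AnapnoGuard cannot occur in a patient who never received it.

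**Working it through.** **Inputs.** From 8.2 and 8.3: bar 0.80, one-sided lower 95% limit, 25 patients per arm. From the total of 60: 30 per arm, assuming equal arms and no dropout. The event rates are assumptions. Section 8.3 names no interval method, so three are shown.

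**The plan's own figures.** The total is consistent with the dropout allowance: 50 / (1 − 0.15) = 58.8, rounded up to 59, against 60 planned. The stated 80% power does not reproduce. Section 8.2 writes "Assuming a true success rate of 80" per cent against a bar of 80%. With p1 = p0 = 0.80,

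power = Φ((p1 − p0 − 1.645·√(p0(1−p0)/n)) / √(p1(1−p1)/n)) = Φ(−1.645) = 5%.

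That is a separate defect, and the endpoint point does not depend on it.

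**Step 1: events the rule tolerates.** Find the smallest x whose lower limit reaches 0.80.

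| n | Method | Smallest passing x (limit) | Next below (limit) | Events allowed |
|---|---|---|---|---|
| 25 | Clopper-Pearson | 24 (0.824) | 23 (0.769) | 1 |
| 25 | Wilson | 24 (0.839) | 23 (0.785) | 1 |
| 25 | Wald | 23 (0.831) | 22 (0.773) | 2 |
| 30 | Clopper-Pearson | 28 (0.805) | 27 (0.761) | 2 |
| 30 | Wilson | 28 (0.817) | 27 (0.774) | 2 |
| 30 | Wald | 27 (0.810) | 26 (0.765) | 3 |

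**Step 2: probability of passing.** P(pass) = P(X ≥ x), with X binomial(n, 1 − event rate). For example, with n = 25, x = 24 and a 2% rate: 25 × 0.98^24 × 0.02 + 0.98^25 = 0.91.

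| Event rate (assumed) | n = 25 (Wald) | n = 30 (Wald) |
|---|---|---|
| 2% | 0.91 (0.99) | 0.98 (1.00) |
| 5% | 0.64 (0.87) | 0.81 (0.94) |
| 10% | 0.27 (0.54) | 0.41 (0.65) |
| 20% | 0.03 (0.10) | 0.04 (0.12) |

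The figure outside the brackets holds for both Clopper-Pearson and Wilson.

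**Step 3: one data set, two answers.** Take an invented result in 25 device patients: one has a device-related event and three others have unrelated events only.
- Device-related definition: 24/25, lower limit 0.824 (Wilson 0.839, Wald 0.896). Pass.
- Any-event definition: 21/25, lower limit 0.670 (Wilson 0.688, Wald 0.719). Fail.

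**Step 4: what the documents say about the all-cause rate.** They give none. The pilot reports related events only. The nearest hint is pilot VAP in one device patient (11%), which is one type of event in very few patients. An 11% event rate would give P(pass) 0.22 (Wald 0.47) at n = 25 and 0.34 (0.58) at n = 30.

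**The case against.** The best case for the protocol is that the unqualified phrases are shorthand. Section 3.1, whose purpose is to define the endpoint, is device-related. Both declared success rules, in the synopsis and in 8.3, refer to attributable events, and the pilot evidence in 8.2 concerns related events only. On that reading the intent is clear and the rest is loose drafting. This stands as a guide to which definition to adopt. It does not settle the matter, because the hypothesis and the proportion actually tested are written without the qualifier in both the synopsis and 8.3.

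Three stronger readings are tempting, and the documents do not support them.
- A reader might infer that the synopsis and 3.1 stand on one side and 8.2 and 8.3 on the other. In fact the synopsis, 8.2 and 8.3 are each internally mixed.
- A reader might infer that the inconsistency reverses the likely conclusion. That needs an all-cause AE rate, which the protocol does not give. At 5% the trial would still more likely pass than fail; at 10% the answer depends on the sample size and the interval; only at about 20% is failure very likely throughout.
- A reader might infer that control success is 100% by definition. That follows only under the AnapnoGuard-attributable wording. The 8.2 control assumption is unqualified, 9.3 lists cuff and suction events as possible in both groups, and the formal test concerns the device arm alone, so no control rate enters it.

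**Conclusion.** The inconsistency is real and concerns the only primary endpoint, so it must be corrected. Its effect is conditional. The rule allows 1 to 3 patients with an event, depending on the evaluable number (25 or 30) and the interval. Moving the event rate from 2% to 20% takes the probability of passing from at least 0.91 to at most 0.12 across all the combinations shown. Where the two definitions would fall on that scale is unknown from the protocol, so the supportable statement is that the choice can reverse the conclusion. The control-arm difficulty is narrower: the attributable wording cannot be used for the comparison that 3.1 asks for, but it leaves the single-arm test untouched.

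**What to change.** - Use one definition in 3.1, 8.2, 8.3 and every synopsis row: the proportion of subjects with no device-related AE or SAE during intubation. State which grades of the 9.3 relatedness scale count as related.
- Reword the 8.3 success rule as the one-sided lower 95% confidence limit of that proportion being at or above 0.80.
- For the comparison with control, judge relatedness to the assigned airway system in both arms. The independent committee that already evaluates events under 9.4 could do this.
- Tabulate all-cause AE and SAE by arm next to the primary result, so that the device-related restriction hides nothing. Section 8.1 already plans tables by arm and relation to treatment.
- A Newcombe interval for the difference between arms is optional and would be descriptive only.

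The cost is wording changes and the relatedness assessment of control-arm events. No change in sample size follows from this point.
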